# A single-center randomized controlled study of intraperitoneal hyperthermic chemoperfusion in combination of recombinant human tumor necrosis factor (TNF) in treatment of malignant ascites caused by advanced abdominal cancers

**DOI:** 10.1097/MD.0000000000031883

**Published:** 2022-12-02

**Keywords:** advanced gynecologic cancers, cisplatin, HIPEC, peritoneal effusion, rmhTNF-NC

## Abstract

**Methods::**

Design and setting: This is a single-center, open trial will be performed in Zhongshan Affiliated Hospital, Guangzhou University of Chinese Medicine.

**Participants::**

Eligible patients will be those with advanced gynecologic cancers and who would be suitable for HIPEC.

**Intervention and Control::**

HIPEC with cisplatin and intraperitoneal perfusion with rmhTNF-NC.

**Co-interventions::**

Further chemotherapy will be offered to patients as per current practice.

Outcomes

Pilot study: Patients and clinicians’ acceptability of the trial to assist in optimization of recruitment.

Primary outcome: One-year overall survival (OS).

Secondary outcomes: Progression-free survival (PFS), adverse events.

Follow-up: One-year follow-up for OS.

Sample size: Twenty patients to demonstrate therapeutic effect of peritoneal effusion caused by OC.

**Discussion::**

This trial will determine the effectiveness of HIPEC with cisplatin and intraperitoneal perfusion with rmhTNF-NC for advanced gynecologic cancers, and guide the optimal treatment for these patients.

## 1. Introduction

According to Global Cancer Statistics 2020, ovarian cancer (OC) is one of the most commonly diagnosed cancer (1.6% of total cases) and one of the leading cause of cancer death (2.1% of the total cancer deaths).^[1]^ OC is the leading cause of mortality among patients bearing gynaecological cancers and the majority of patients are diagnosed in advanced stages.^[2]^ At present, the standard first-line treatment for OC is cytoreductive surgery followed by platinum-based combination chemotherapy, which is basically the same as fallopian tube or primary peritoneal cancer.^[3–5]^ Malignant ascites refers to peritoneal effusion caused by primary peritoneal or other malignant tumors that metastasize to the peritoneum.^[6]^ Malignant peritoneal effusion is common in OC, and about 10% of OC patients are faced with recurrence and metastasis. Tumor cells in OC-associated malignant ascites promote disease recurrence and patient mortality is mainly associated with widespread metastasis to serosal surfaces and accompanying peritoneal effusions.^[7]^

There is no consensus on systematic treatment of malignant ascites in patients with advanced OC.^[8]^ Hyperthermic intraperitoneal chemotherapy (HIPEC) has been widely used in the treatment of advanced OC. At the same time, recombinant human tumor necrosis factor for injection (rmhTNF-NC) has been proved to be effective in treating thoracic and abdominal effusion caused by advanced tumors by a number of studies. In addition, there is no study, either prospective or retrospective, involving HIPEC combined with rmhTNF-NC in the treatment of abdominal effusion caused by advanced OC, and therefore, we designed a single-arm phase I trial to explore the efficacy of it.

## 2. Design

This clinical trial is a single-center exploratory single-arm study approved by the Ethics Review Committee of Zhongshan Affiliated Hospital, Guangzhou University of Chinese Medicine (Approval Number: 2021ZSZY-LLK-163). The trial is registered at chictr.org.cn (ChiCTR2100045155, May 7, 2021). The trial will be conducted in accordance with the Declaration of Helsinki (64th version, October 2013) and the guidelines for Good Clinical Practice (GCP). The in-and exclusion criteria are summarized in Table 1.

**Table 1 T1:** In- and exclusion criteria.

Inclusion criteria	Exclusion criteria
Pathologically or cytologically confirmed ventral or pelvic malignancy, positive peritoneal metastasis of these cancer or positive exfoliated cells of these cancer were detected in peritoneal lavage fluid	Drug allergy history of TNF and its derivatives
Moderate or greater amount of peritoneal effusion. Definition of moderate ascites, ultrasonic examination of ascites in decubitus position (≥3 cm); accompanied with clinical symptoms (abdominal distension and discomfort)	Pregnant or lactating women, women of child-bearing age who were not willing to use contraception during the study period; or men are unwilling to use effective contraceptives during treatment and for the next year
Aged 18‐75 years male or non-pregnant or lactating women	Patients with severe or uncontrolled medical diseases and infections (including atrial fibrillation, angina pectoris, cardiac insufficiency, ejection fraction less than 50%, uncontrollable hypertension, body temperature > 38 °C, etc)
Bone marrow reserve function is good, blood routine meets the following conditions: white blood cell (>3.5 * 10^9/L), neutrophil (>1.5 * 10^9/L), platelet(>100 * 10^9/L), hemoglobin (>90 g/L)	Encapsulated peritoneal effusion
Good organ function, biochemical examination met the following conditions: ALT < 2.5 * ULN, AST < 2.5 * ULN, serum total bilirubin < 1.5 * ULN, serum creatinine < 1.5 * ULN	Severe hypoproteinemia
ECOG <= 1	HIV positive and active hepatitis
Voluntary signing of informed consent	Patients with severe or uncontrollable mental illness
	Any condition that is unstable or that could jeopardize the safety of the subject and their compliance in the study

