### 2.4. Primary and secondary objectives

Primary objectives: HIPEC effectiveness in the combined treatment of rmhTNF-NC in abdominal effusion caused by advanced OC will be analyzed. The response will evaluated according to the WHO criteria^[9]^ and will classify as complete response (CR): the abdominal effusion disappeared completely and lasted for more than 4 weeks, partial response (PR): more than 50% less effusion than before treatment (based on the maximum depth of effusion observed by B-ultrasound examination), stable disease (SD): fluid accumulation should be reduced by less than 50% or increased by less than 25% from before treatment (based on the maximum depth of fluid accumulation observed by B-ultrasound examination), and progressive disease (PD): Fluid accumulation increased by more than 25% compared with before treatment. Objective response rate (ORR) calculated by CR + PR. Disease control rate (DCR) calculated by CR + PR + SD. The evaluation of adverse reactions was divided into grade 0 to 4 according to NCI CT CAE 4.0.

Secondary objective: Quality of life (QoL), QoL was assessed with the European Organization for Research and Treatment for Cancer Quality of Life Questionnaire core 30 (EORCT QLQ-C30) by the dietician before HIPEC and 1 month after HIPEC.

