## 4. Conclusion

rmhTNF-NC and HIPEC with cisplatin is effective while treating patients with abdominal effusion caused by advanced OC, we will conduct a multicenter randomized controlled trial next, which may help expand the indication of HIPEC and is expected to provide an evidence-based basis for reducing mortality and improving QoL in patients with advanced OC.

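### The protocol states three different populations, so its 20 patients are not ensured to answer the ovarian-cancer question in the primary objective

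*Protocol article*

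**What the plan says.** The inclusion criteria in section 2 (Design), Table 1, ask for "Pathologically or cytologically confirmed ventral or pelvic malignancy" with peritoneal spread. They set no ovarian or gynecologic restriction. The age and sex criterion reads "years male or non-pregnant or lactating women", and the exclusion criteria list the case where "men are unwilling to use effective contraceptives during treatment and for the next year". The title agrees with this breadth: "treatment of malignant ascites caused by advanced abdominal cancers".

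The abstract is narrower: "Eligible patients will be those with advanced gynecologic cancers and who would be suitable for HIPEC". Its discussion paragraph and the keywords also refer to gynecologic cancers.

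Four places are narrower still and name ovarian cancer (OC): the rationale at the end of section 1, the abstract's sample-size line, the primary objective in section 2.4 ("HIPEC effectiveness in the combined treatment of rmhTNF-NC in abdominal effusion caused by advanced OC will be analyzed") and section 4, which speaks of "patients with abdominal effusion caused by advanced OC" and announces a multicentre randomised trial directed at advanced OC.

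Section 2.1 fixes enrolment at 20 and gives no number or share of ovarian patients. Section 2.5 defines the full analysis set (FAS), which carries the main results, by receipt of study drug and at least one post-treatment measurement. The per-protocol set adds, among other things, conformity with the eligibility criteria. Neither set refers to tumour type.

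**The concern.** The population is part of what a primary result means. Here the objective and the eligibility table describe different groups, and the analysis set does not bring them back together. A site that follows Table 1 may enrol a man, or a woman with a non-gynecologic abdominal tumour. That patient enters the FAS and counts in the objective response rate (ORR), which section 2.4 ties to OC.

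Two things are at stake. The pooled ORR would carry an ovarian label it may not deserve, and section 4 intends to build the next trial on it. If a reader instead extracts the ovarian patients, their number is left to chance and the estimate could be much less precise than 20 patients suggest.

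The problem does not depend on ORR being the primary outcome. It is the same for the one-year overall survival that the abstract names as primary.

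**Working it through.** **Step 1: the passages side by side.**

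| Place | Population |
|---|---|
| Title | Advanced abdominal cancers |
| Section 2, Table 1 | Any abdominal (printed as ventral) or pelvic malignancy; men and women |
| Abstract (participants, discussion), keywords | Advanced gynecologic cancers |
| Section 1, rationale | Advanced OC |
| Abstract, sample-size line | OC, 20 patients |
| Section 2.4, primary objective | Advanced OC |
| Section 4, conclusion and next trial | Advanced OC |

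The title and Table 1 nearly coincide, so this is three populations.

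**Step 2: can one reading reconcile them?** Reading the Table 1 tumour wording as shorthand for OC fails, because Table 1 refers to men twice, once in inclusion and once in exclusion, and men cannot have OC. Reading OC in section 2.4 as shorthand for all abdominal tumours fails, because section 1 introduces OC as the abbreviation for ovarian cancer.

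**Step 3: does the analysis restore the ovarian question?** The FAS depends on exposure and measurement, and the per-protocol set on the same criteria. Section 2.5 plans a logistic regression of factors affecting response but names no factors. Even with tumour type as a covariate, it would not turn the pooled ORR into an ovarian ORR.

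**Step 4: the plan's own figure.** The 20 patients cannot be reproduced, because the article gives no null rate, target rate, power or precision for them. The number is therefore neither confirmed nor refuted, and no corrected number can be derived.

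**Step 5: illustration of precision.** Inputs: total n = 20 (section 2.1). The ovarian counts of 20, 10 and 6 and the ORR of 50% are assumptions. The exact (Clopper-Pearson) 95% limits for x responders among n are:

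- lower = 2.5% quantile of Beta(x, n − x + 1)
- upper = 97.5% quantile of Beta(x + 1, n − x)

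| Ovarian patients (assumed) | Responders (assumed 50%) | Exact 95% CI | Width |
|---|---|---|---|
| 20 | 10 | 27.2% to 72.8% | 45.6 points |
| 10 | 5 | 18.7% to 81.3% | 62.6 points |
| 6 | 3 | 11.8% to 88.2% | 76.4 points |

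**Step 6: illustration of pooling.** Pooled ORR = s × (ovarian ORR) + (1 − s) × (other ORR), with s the ovarian share. Assume s = 0.5 and an ovarian ORR of 60%:

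- other ORR 30%: 0.5 × 60% + 0.5 × 30% = 45%
- other ORR 80%: 0.5 × 60% + 0.5 × 80% = 70%

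So under these assumptions the pooled figure could lie 15 points below or 10 points above the ovarian one. If the two rates are equal there is no shift.

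**The case against.** Several points on the other side are fair.

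- **Case mix.** A reader might infer that the 20 patients do not answer the ovarian question. The documents do not show that: the case mix is unknown, and all 20 could turn out to have OC. What stands is that nothing ensures it.
- **Which text governs.** Section 2 says Table 1 summarises the criteria, and the abstract describes eligibility differently. The article does not say which prevails. Table 1 is the most detailed rule shown, but that uncertainty is itself part of the contradiction.
- **Left to another document.** Subgroup analyses by tumour type are commonly specified in an analysis plan that is not shown. Their absence here is no finding. An analysis plan could define an ovarian subset, but it could not make Table 1 agree with section 2.4.
- **Evidence that tumour types differ.** Section 3.1 reports a survival gain with HIPEC in ovarian disease and none in colorectal disease. A reader might infer from this that pooling biases the ORR. It does not support that: the contrast concerns overall survival rather than effusion response, and section 3.1 itself says the colorectal result may reflect the treatment parameters. The response rates in section 3.2 are split by pleural and abdominal site, not by primary tumour. The size of any pooling bias is therefore unknown.
- **Exploratory setting.** Enrolling mixed tumours in a small single-arm ascites study is legitimate, and even 20 ovarian patients give a wide interval. That is true, but the fault lies in the mismatch with the objective, not in mixed enrolment.

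**Conclusion.** The contradiction is in the current text and depends on no assumption: three populations are stated, and the eligibility table is wider than the population of the primary objective. As written, the trial may report a mixed-tumour response rate as an ovarian-cancer result and carry it into an ovarian-cancer randomised trial.

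The size cannot be fixed from the document. At an assumed 50% ORR, the ovarian interval widens from about 46 points with 20 ovarian patients to about 63 with 10 and about 76 with 6. The 45% to 70% pooled range likewise rests on assumed rates and an assumed half share. These figures show scale only. This should be corrected before results are reported.

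**What to change.** Reconcile the places in the table above so that one population governs throughout.

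**Cheapest, and workable whoever is already enrolled** (section 2.1 has treatment starting by the end of 2021): keep Table 1. Restate the abstract, keywords, rationale, sample-size line, objective and conclusion as malignant ascites from abdominal or pelvic cancers. Report ORR with exact 95% CI overall and by primary tumour, with ovarian cancer named as a descriptive subgroup and its number of patients given. No new data are needed beyond recording the primary tumour. The work is mostly wording, but it changes the population of a stated primary objective, so it should be dated, explained and carried to the registration and the ethics committee. The downside is that the conclusion is no longer specific to ovarian cancer and the ovarian estimate is less precise than one from 20 ovarian patients.

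**If the ovarian question must stand:** bring Table 1 (tumour type, male eligibility and the contraception rule for men), the title and the abstract into line with the objective. Alternatively, leave enrolment as it is, limit the primary analysis to ovarian-cancer patients and state their number. The first route needs an eligibility amendment, is likely to slow accrual and may come too late for patients already enrolled. The second leaves fewer than 20 in the primary analysis unless every patient has OC.

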### 2.1. Start trial

Inclusion, treatments started in Zhongshan Affiliated Hospital, Guangzhou University of Chinese Medicine by the end of 2021. Twenty patients will be enrolled in this trial.

### 2.2. Therapeutic method

After ascites was extracted as far as possible, the patients were treated by HIPEC combined with intracavity injection of rmhTNF-NC. The specific treatment methods were as follows: d1 and d4 were given cisplatin at a dose of 30 mg/m^2^, and the cisplatin and 2000 to 3000 mL 0.9% normal saline were added into a special treatment bag for body cavity thermoperfusion chemotherapy, and then the air in the bag was drained. The treatment bag was connected with the coelomic thermal perfusion therapy machine. After the liquid medicine in the treatment bag was heated to 43 °C, the machine was connected with the abdominal drainage catheter placed in the patient, and the coelomic circulation thermal perfusion therapy was carried out on the patient. D7 was mixed with 20 mL 0.9% normal saline, 10 mg dexamethasone and 3 million IU rmhTNF-NC, and injected into the abdominal cavity through abdominal drainage catheter. Between 2 and 4 hours after the infusion, the patient was asked to change his position every 15 minutes so that the solution was evenly distributed in his abdominal cavity.

### 2.3. Follow-up

During follow-up before and after the completion of HIPEC, physical examinations and measurements of white blood cell count, Hemoglobin, neutrophil count, blood platelet count, liver enzymes and serum creatinine levels were performed and then every 1 month for abdominal ultrasonography until the one-year point.

### 2.4. Primary and secondary objectives

Primary objectives: HIPEC effectiveness in the combined treatment of rmhTNF-NC in abdominal effusion caused by advanced OC will be analyzed. The response will evaluated according to the WHO criteria^[9]^ and will classify as complete response (CR): the abdominal effusion disappeared completely and lasted for more than 4 weeks, partial response (PR): more than 50% less effusion than before treatment (based on the maximum depth of effusion observed by B-ultrasound examination), stable disease (SD): fluid accumulation should be reduced by less than 50% or increased by less than 25% from before treatment (based on the maximum depth of fluid accumulation observed by B-ultrasound examination), and progressive disease (PD): Fluid accumulation increased by more than 25% compared with before treatment. Objective response rate (ORR) calculated by CR + PR. Disease control rate (DCR) calculated by CR + PR + SD. The evaluation of adverse reactions was divided into grade 0 to 4 according to NCI CT CAE 4.0.

Secondary objective: Quality of life (QoL), QoL was assessed with the European Organization for Research and Treatment for Cancer Quality of Life Questionnaire core 30 (EORCT QLQ-C30) by the dietician before HIPEC and 1 month after HIPEC.

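### Partial response has no duration and no fixed baseline scan, so in an uncontrolled trial that drains ascites first, fluid removed by catheter can count towards ORR

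*Protocol article*

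**What the plan says.** The treatment section (2.2) puts drainage first: "After ascites was extracted as far as possible, the patients were treated by HIPEC combined with intracavity injection of rmhTNF-NC". Perfusion with cisplatin follows on days 1 and 4, and rmhTNF-NC on day 7.

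Section 2.4 grades response by fluid. CR means "the abdominal effusion disappeared completely and lasted for more than 4 weeks". The next category is "partial response (PR): more than 50% less effusion than before treatment (based on the maximum depth of effusion observed by B-ultrasound examination". Progression is "Fluid accumulation increased by more than 25% compared with before treatment". The summary measure is "Objective response rate (ORR) calculated by CR + PR".

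Three other places bear on this:

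- Table 1 (section 2) sets the entry threshold by "ultrasonic examination of ascites in decubitus position (≥3 cm".
- Section 2.3 plans follow-up, "then every 1 month for abdominal ultrasonography until the one-year point". It does not name the scan that decides response.
- The abstract, under co-interventions, states: "Further chemotherapy will be offered to patients as per current practice".

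Section 2 describes the trial as single-arm. Section 2.1 gives 20 patients.

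**The concern.** The endpoint measures how much fluid is present, and the first step of the procedure removes fluid. The response definition does not separate the two.

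Two features of the wording cause this. The reference reading is described only as before treatment, and it is not placed before or after the drainage. PR also carries no duration, while CR in the same sentence must persist for more than 4 weeks. Since ORR adds the two, the weaker condition governs entry to the responder group, and one low reading among the monthly scans is enough.

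A randomised control arm drained in the same way would absorb much of this, but the trial has none. Whatever drainage contributes to the observed ORR will be read as the effect of HIPEC plus rmhTNF-NC. Section 2.4 places effusion response under the primary objectives, so the trial's main efficacy statement is affected.

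**Working it through.** The article gives no target ORR, power or derivation for its 20 patients, so there is no stated figure to reproduce. The check applies the article's thresholds to readings that the definitions allow.

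**Inputs from the article.** PR: depth below 0.5 × baseline. PD: depth above 1.25 × baseline. Entry depth: at least 3 cm. CR duration: more than 4 weeks. PR duration: none stated. Scans: monthly to one year. Arms: one.

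**1. Baseline taken before drainage.** At the entry minimum the PR limit is 0.5 × 3 cm = 1.5 cm and the PD limit is 1.25 × 3 cm = 3.75 cm. If drainage takes the depth below 1.5 cm and it is still below that at one monthly scan, the patient is a PR whether or not the drugs did anything. The same holds for a scan taken soon after a repeat drainage.

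**2. Baseline taken after drainage.** Assume 1 cm remains. The PR limit is 0.5 × 1 = 0.5 cm and the PD limit is 1.25 × 1 = 1.25 cm.

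**3. One patient under both readings.** Assume entry at 3 cm, 1 cm left after drainage, and 1.3 cm at a later scan.

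- Against the pre-drainage depth: 1 − 1.3/3 = 56.7% less fluid, a PR.
- Against the post-drainage depth: 1.3/1 − 1 = 30% more fluid, a PD.

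The words allow both. The first is the more natural, because the entry scan is the only pre-treatment ultrasound that the article describes.

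**4. CR and PR side by side.** A patient whose fluid disappears for one scan and then returns is not a CR, because the 4-week condition fails. That same scan shows more than 50% less fluid, so it meets the PR definition and the patient still enters ORR. The duration rule for CR therefore does not protect ORR.

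**5. How misclassification would move ORR (illustration only).** Let t be the true response rate and q the share of true non-responders scored PR through drainage or later chemotherapy. Then apparent ORR = t + (1 − t)q. The article gives no q, so a range is shown. For t, one column uses 46.03%, the abdominal-effusion ORR that section 3.2 reports from a phase IV study of rmhTNF-NC monotherapy. The other uses an assumed 30%.

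| q (assumed) | apparent ORR, t = 46.03% | expected responders of 20 | apparent ORR, t = 30% |
|---|---|---|---|
| 0% | 46.0% | 9.2 | 30% |
| 10% | 51.4% | 10.3 | 37% |
| 20% | 56.8% | 11.4 | 44% |
| 30% | 62.2% | 12.4 | 51% |
| 50% | 73.0% | 14.6 | 65% |

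For example, at q = 20%: 0.4603 + 0.5397 × 0.20 = 0.568, and 20 × 0.568 = 11.4. The table shows sensitivity. It does not estimate the bias in this trial.

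**6. Can the planned scans confirm PR?** Monthly scans are on average 365/12 = 30.4 days apart, against 28 days in 4 weeks. Two consecutive scans therefore normally show a duration of more than 4 weeks without any added visit.

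**The case against.** The strongest reply has four parts.

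*The article is condensed and cites WHO criteria.* The deciding visit and the handling of repeat drainage may stand in the full protocol, and the cited criteria may require confirmation. Neither is at hand. This is fair for those details, and their absence alone would not be a finding. But the article does state the response definition, with thresholds, method and a duration for CR, and that stated rule is what lets a single low scan count.

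*Drainage alone is not scored.* The full analysis set needs a main measurement after treatment, treatment runs to day 7, and the ultrasounds are monthly. A scan straight after the first drainage therefore decides nothing, and fluid may have returned by the first monthly scan. This stands and limits the bias. It does not remove it, because slow re-accumulation and repeat drainage remain possible and any single later scan may qualify.

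*The size is unknown.* This stands. A reader might infer that ORR could be near 100% or near 0% in the same patients depending on the baseline. The near-0% branch needs a post-drainage baseline, which the entry scan makes the less natural reading. A reader might also compute that, if 80% or 90% of patients stay below half depth, 14 or more of 20 respond with probability 0.913 or 0.998. Those shares are assumed, and 14 of 20 is not a rule of this trial, so the documents do not support such a claim.

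*ORR may not be primary.* The abstract names one-year overall survival as the primary outcome, while section 2.4 puts effusion response under primary objectives. The weight of this point depends on which governs. ORR is the only efficacy measure that section 2.4 defines alongside disease control, and the conclusion in section 4 is about effusion.

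**Conclusion.** The concern holds as a defect in a stated definition. After maximal drainage, PR is judged against an unanchored reading and without the persistence required of CR. In a single-arm trial, one low scan reflecting initial or repeat drainage can therefore add to ORR. The threshold arithmetic is firm: at 3 cm entry depth, anything under 1.5 cm is a PR.

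The size of the bias cannot be derived from the documents. It depends on how fast fluid returns, how often drainage is repeated and which scan is used. Re-accumulation before the first monthly scan would make it smaller.

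A reader might go further and treat every response after further chemotherapy as false. The article offers such chemotherapy as current practice, so scoring all of it as non-response could make ORR follow the timing of chemotherapy. Separate reporting is better supported.

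**What to change.** In section 2.4:

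- Define baseline as the last ultrasound depth before drainage, for PR, SD and PD alike.
- Require PR, like CR, to last more than 4 weeks, shown on consecutive planned monthly ultrasounds. If two scans fall 28 days or less apart, use the next one.
- Count a repeat drainage before confirmation as non-response. This classifies the endpoint only and does not affect when a patient may be drained.
- Report ORR with and without responses first confirmed after further systemic chemotherapy.
- Keep unconfirmed ORR as a secondary figure, for comparison with published rates.
- State in the conclusion that drainage and drug effects cannot be fully separated without a control arm. A pre-drainage baseline still includes the drainage in the fall.

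**Cost.** No extra scans are normally needed. The confirmed ORR may be lower and less comparable with published unconfirmed rates. Section 2.1 indicates that treatment started by the end of 2021 and the article appeared in December 2022, so enrolment has begun. The change must be documented as an amendment to an endpoint definition, stating what response data had been seen by then.

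### Partial response rests on ultrasound depth alone, with no duration or drainage condition, so a patient whose ascites returns and is drained shortly before a scan can be scored a responder

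*Protocol article*

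**What the plan says.** Section 2.4 of the protocol article makes the effect on abdominal effusion the primary objective and gives a cut-off for each response category. (The abstract names one-year overall survival as primary; that discrepancy is a separate matter.)

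- A partial response (PR) is set out as "more than 50% less effusion than before treatment (based on the maximum depth of effusion observed by B-ultrasound examination".
- Under progressive disease (PD) the article puts this: "Fluid accumulation increased by more than 25% compared with before treatment".
- Between those two lies stable disease (SD), a reduction of under 50% or a rise of under 25%, on the same depth measure as PR.
- A complete response (CR) needs more, namely that "the abdominal effusion disappeared completely and lasted for more than 4 weeks".

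The summary measures follow directly: "Objective response rate (ORR) calculated by CR + PR", and DCR adds SD. Only CR carries a time condition.

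For follow-up, section 2.3 provides blood tests and examinations, "then every 1 month for abdominal ultrasonography until the one-year point". Drainage appears only in section 2.2, as the initial removal of fluid ("After ascites was extracted as far as possible, the patients were treated by HIPEC combined with intracavity injection of rmhTNF-NC") and as the route of treatment, where "the machine was connected with the abdominal drainage catheter placed in the patient". No section says how response is scored after a later therapeutic drainage. Section 2.5 carries the last observation forward (LOCF) when the course is incomplete, with no exception for a reading taken after a drainage.

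**The concern.** Depth on ultrasound shows whether treatment controlled the ascites only if nothing else has removed the fluid. A therapeutic drainage during follow-up removes it mechanically. A scan soon afterwards then measures the drainage, and the PR rule credits the fall to the study treatment.

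The situation is plausible here. Patients enter with symptomatic ascites of moderate or greater amount (Table 1: "ultrasonic examination of ascites in decubitus position (≥3 cm") and are followed for a year. The study is open and has no control arm, so the error cannot cancel in a comparison. It runs in one direction for ORR, because draining a non-responder before a scan can only move the patient towards response. The article's conclusion looks ahead to a multicentre randomized trial, so an inflated ORR could affect that decision.

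**Working it through.** The article gives no null rate, target rate or power for the 20 patients, so there is no planned figure to reproduce. The check applies the section 2.4 cut-offs to example depths and then shows the possible size at n = 20.

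**Classification.** Change = (depth at scan − depth before treatment) / depth before treatment. The depths are illustrative, chosen to respect the 3 cm entry minimum.

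| Before treatment | Situation at scan | Depth | Change | Category |
|---|---|---|---|---|
| 6 cm | refilled, then drained | 1.5 cm | (1.5 − 6)/6 = −75% | PR |
| 6 cm | refilled, then drained | 2 cm | (2 − 6)/6 = −67% | PR |
| 6 cm | refilled, scanned before drainage | 6 cm | 0% | SD |
| 6 cm | refilled, scanned before drainage | 8 cm | (8 − 6)/6 = +33% | PD |
| 3 cm | refilled, then drained | 1 cm | (1 − 3)/3 = −67% | PR |
| 3 cm | refilled, partly drained | 2 cm | (2 − 3)/3 = −33% | SD |

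The same clinical course can therefore be PR, SD or PD, depending on whether the scan falls before or after the drainage and how complete the drainage was. If the post-drainage scan is the patient's last, LOCF carries PR to the final result.

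**Effect on ORR.** One patient is 1/20 = 5 percentage points. For illustration, take the 46.03% that the article's discussion cites for rmhTNF-NC alone in abdominal effusion: 0.4603 × 20 = 9.2, about 9 responders (45%). Two misclassified patients give 11/20 = 55%; four give 13/20 = 65%.

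Alternatively, let q be the share of true non-responders who are drained before the scan and scored PR. Expected ORR = 0.4603 + (1 − 0.4603) × q. The last column is the exact binomial chance of at least 14/20, the smallest count whose upper tail under 46.03% is below 5% (13/20 has 7.0%). The article sets no such threshold.

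| q | Expected ORR | Chance of ≥14/20 |
|---|---|---|
| 0 | 46.0% | 2.7% |
| 10% | 51.4% | 7.4% |
| 20% | 56.8% | 16.8% |
| 30% | 62.2% | 31.9% |

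**Effect of the correction.** With exact 95% intervals, an observed 12/20 = 60% (36% to 81%) becomes 10/20 = 50% (27% to 73%) if two responders are reclassified, and 8/20 = 40% (19% to 64%) if four are.

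**Effect on DCR.** SD already counts as control. From 6 cm, the SD limit is 6 × 1.25 = 7.5 cm. A refill below that, wrongly scored PR after drainage, leaves DCR unchanged. Only a refill above 7.5 cm, which should have been PD, raises DCR when the drained reading is used.

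**The case against.** The strongest objection is that this argues from silence. The article never says that a drained patient counts as a responder. It refers to WHO criteria that are not reproduced, and the full protocol or analysis plan, not shown, may say how such events are scored. That stands against the stronger reading, that every re-drained patient is scored a responder. It does not remove the point, because the article does not defer the definition: it states each category with its cut-off, and PR as stated admits the drained patient.

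Several limits on the mechanism also stand. B-ultrasound depth is named for PR and SD but not for CR or PD. No scan is named as the one that decides response, so the text does not confine assessment to the monthly scans. A scan before the drainage, or after a partial one, can give SD or PD. CR is partly protected by its four-week condition, although a return and drainage between monthly scans could be missed. Remaining PR all year would need a drainage shortly before each scan.

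On size, the documents give no repeat-drainage rate, and 46.03% belongs to a different regimen. On DCR, the only cited figure is 97.27%, for pleural and abdominal effusion pooled. If it applied, about 20 × (1 − 0.9727) = 0.5 patients would be PD, which leaves little room for upward bias.

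Finally, calling any drainage after day 7 permanent PD would contradict the article's own PD cut-off and erase responses already documented. That objection is right, and the fix below avoids it.

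**Conclusion.** The concern holds in a limited form. As written, the PR rule can turn a failure of ascites control into an objective response when a therapeutic drainage shortly precedes a scan. The bias in ORR is upward, 5 percentage points per such patient at n = 20. The range of 55% to 65%, and the results for q of 10% to 30%, rest on assumed drainage counts and a borrowed starting rate; they show scale and are not a forecast.

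A reader might infer that DCR is inflated to the same degree, or that the distortion could reach tens of points. The documents support neither. DCR moves only where the refill exceeded the depth before treatment by more than 25%. A very large shift in ORR would need many true non-responders, all drained below half their starting depth just before the deciding scan.

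The priority is moderate: this is an exploratory study with no stated decision threshold, but the gap affects the section 2.4 primary objective.

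**What to change.** Add a scoring rule to section 2.4. It concerns classification only and leaves the decision to drain with the clinician.

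1. Record the date, volume and reason of every therapeutic ascites drainage after the day 7 injection.
2. Do not use scans after such a drainage to assign CR, PR or SD, whether directly or through LOCF.
3. For ORR, count a patient with no qualifying response documented before the drainage as a non-responder, kept in the denominator. Keep a response that met its definition before the drainage, with its end dated at the drainage.
4. For DCR, classify from the last depth measured before the drainage under the existing cut-offs, and report DCR also with repeat drainage counted as failure. State how many drained patients had no post-treatment depth before the drainage, since for them only the second version is informative.

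The cost is a short addition to the endpoint definition and a case report form entry, with no extra procedure. The downside is that the reported ORR may be lower. If the full protocol or analysis plan already contains such a rule, citing it in section 2.4 is enough.
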